|----------------------------------------------------------------------------------------------------------------------------------------------------------------------------------------------------------------------------------------|------------------------------------------------------------------------------------------------------------------------------------------------------------------------------------------------------------------------------------------------------------------------------------------------------------------------------------------------------------------------------------------------------------------------------------------------------------------------------------------------------------------------------------------------------------------------------------------------------------------------------------------------------------------------------------------------------------------------------------------------------------|
| 
 
To test whether any of the experimental interventions decrease resolution rate for symptomatic SARS-CoV-2 infection / COVID-19 disease
 
                                               | 
 
Proportion of days with fever after randomization
 
Proportion of days with respiratory symptoms after randomization
 
Time until clinical improvement (up to 28 days), defined normalization of temperature, respiratory rate, SaO2, and cough relief (> 50 in relation to baseline measured on a visual analog scale) in the last 72 hours;
 
Reduction in the perception of dyspnea (upper respiratory tract respiratory symptoms scale - WURSS-11) on days 0, 3, 7, 14 and 28 days;
 
Time to clinical failure, defined as time to need for hospitalization due to dyspnea, death, need for mechanical ventilation, shock with need for vasoactive amines;
 
 |

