#### **Primary analyses:**

The primary analyses will be conducted on the ITT population overall and by cohort. Participants randomized to each active arm will be compared to participants randomized to placebo (ascorbic acid). The primary analysis will make use of all participants randomized to placebo, whether contemporaneously enrolled or not using an Empirical Bayesian information borrowing method (described below). Due to anticipated heterogeneity in risk of disease progression, pre-specified baseline variables, including age, weight, and days of symptoms at time of enrollment will be included in the model to increase precision.

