#### **12.3.2. Secondary endpoints**

All secondary endpoints will be assessed in the Intention-to-Treat population overall and by cohort.

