##### **12.3.2.3. Symptom Resolution**

Days with fever after randomization, respiratory symptoms (ordinal outcome) after randomization after randomization will be modeled using proportional odds regression method stratified by site.

The procedure assumes multinomial distributions for the marginal (i.e., time-specific) univariate ordinal responses and uses a working correlation structure to account for within-subject association between the repeated measures. Time-dependent covariates (e.g. ordinal responses at previous timepoints) will be included the statistical model.

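### The symptom model conditions on each patient's own earlier post-randomisation responses, so its treatment odds ratio is a transition effect and not the total effect on symptoms

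*Protocol*

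**What the plan says.** Section 12.3.2.3 states that fever and respiratory symptoms after randomisation "will be modeled using proportional odds regression method stratified by site". It describes the target as marginal: "The procedure assumes multinomial distributions for the marginal (i.e., time-specific) univariate ordinal responses". It says the method "uses a working correlation structure to account for within-subject association between the repeated measures". It then closes with "Time-dependent covariates (e.g. ordinal responses at previous timepoints) will be included the statistical model".

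Nothing in the section limits those earlier responses to the baseline value, and nothing says that results will be averaged over them to recover an effect by arm.

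Three other places bear on the point. The endpoints in section 4.1 include "Proportion of days with respiratory symptoms after randomization". Section 12.3.2 says "All secondary endpoints will be assessed in the Intention-to-Treat population overall and by cohort". For the primary analysis, section 12.3.1 names covariates fixed before treatment: "pre-specified baseline variables, including age, weight, and days of symptoms at time of enrollment will be included in the model to increase precision".

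**The concern.** Study drug starts on the day of randomisation (Schedule of Activities, note 9), and symptoms are reviewed repeatedly from then on. A response at an earlier follow-up visit is therefore already an outcome of treatment. If the drug improves symptoms by day 3 and the improvement lasts, a model for day 7 that conditions on day 3 credits the drug only with what it added between the two visits. The benefit present at day 3 is absorbed by the covariate.

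At stake is the meaning and size of the reported symptom odds ratio. A reader of an intention-to-treat analysis would take it as the effect of assignment on symptoms. It would be a different quantity, and in the scenarios examined a smaller one.

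**Working it through.** **The two models.** Let A be the arm, Y_0 the baseline response and Y_t the response at visit t.

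- Marginal: logit P(Y_t > k) = visit_t − c_k + βA + g(Y_0). Here β is the total effect on symptoms at a visit.
- With lag: logit P(Y_t > k | Y_{t−1}) = visit_t − c′_k + θA + g′(Y_0) + h(Y_{t−1}). Here θ is the effect on the current state given the previous one.

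The first three statements of 12.3.2.3 describe β; the last yields θ. The working correlation already handles dependence between visits, so the lag is not needed for that purpose.

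**How many lags are post-randomisation.** Section 4.1 schedules its dyspnoea scale "on days 0, 3, 7, 14 and 28 days". On that grid there are four follow-up assessments. The lag for day 3 is day 0, which is harmless. The lags for days 7, 14 and 28 are days 3, 7 and 14, so 3 of 4 are post-randomisation.

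**Size.** The protocol states no figure for this model, so there is none to reproduce. Effect size, score levels and correlation had to be assumed. The main check used a 4-level outcome, baseline plus four follow-ups, 8,000 patients per arm to limit sampling noise, one data set per scenario and an independence working correlation. Both fits include visit and the baseline response. Shrinkage = 1 − (log OR with lag) / (log OR without lag).

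| Assumed scenario | Log OR, baseline only | Log OR, baseline + lag | Shrinkage | OR |
|---|---|---|---|---|
| Constant effect, patient random effect SD 1.0 | −0.426 | −0.382 | 10% | 0.65 → 0.68 |
| Same, SD 1.5 | −0.401 | −0.339 | 15% | 0.67 → 0.71 |
| Same, SD 2.5 | −0.355 | −0.277 | 22% | 0.70 → 0.76 |
| Markov, effect −0.3 at every step, dependence 0.8 | −0.386 | −0.303 | 22% | 0.68 → 0.74 |
| Markov, effect −0.3 at every step, dependence 1.3 | −0.400 | −0.298 | 26% | 0.67 → 0.74 |
| Markov, effect −0.8 before first follow-up only, dependence 1.3 | −0.422 | −0.238 | 44% | 0.66 → 0.79 |
| No effect (SD 1.5) | −0.025 | −0.020 | – | – |

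Two rows show the mechanism. With an effect of −0.3 at every step, the lagged model returns about −0.30: it estimates the per-step effect correctly and omits what has accumulated. With an effect of −0.8 at one of four steps, the average step effect is −0.8 / 4 = −0.20, and the lagged model gives −0.238.

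A second set of assumptions used a 3-level score, four visits and a constant 0.2 SD latent shift, with 12,000 per arm. Shrinkage was 17% to 29% without the baseline response in the models and 26% to 35% with it, which lies inside the range above.

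**Consistency.** With a non-independence working correlation, the estimating equations combine the residual at one visit with covariates from other visits. Today's response is the next visit's covariate, so the residual and that covariate are correlated and the estimates can be inconsistent. This is a theoretical point; all the fits above used independence, where it does not arise.

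**The case against.** The strongest reply is that a proportional-odds model conditioned on the previous response is a recognised transition model. It estimates its own quantity correctly, and it can be averaged back to time-specific probabilities by arm. Section 12.3 calls itself a summary and leaves the detailed methods to a statistical analysis plan that is not at hand. The objective speaks of a rate of resolution, which could be read as a transition quantity. Much of this stands. A reader might infer that the odds ratio is simply biased, but the protocol does not say which quantity will be reported. It misleads only if θ is presented as the total effect. Against the reply, the inclusion is stated affirmatively, no averaging is mentioned, the model is called marginal, and the listed endpoints include proportions of days, which are not transition quantities.

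A second reply is that odds ratios are non-collapsible, so coefficients from different covariate sets are not strictly comparable. That limits the precision of any percentage, but it does not explain the direction. Adding the baseline response moved the log odds ratio away from zero in the constant-effect scenarios (−0.413 to −0.426, −0.367 to −0.401, −0.293 to −0.355). Adding the lag moved it back toward zero.

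Other stronger readings are not supported:

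- **Fever.** If days with fever is one total per patient, as the wording suggests, there is no earlier response to include.
- **Inconsistent estimates as a settled fault.** The protocol does not name the working correlation.
- **Early and lasting symptom benefit as the trial's hypothesis.** The amendment rationale argues for starting early to prevent progression; it does not describe the course of a symptom benefit.
- **A single narrow loss figure.** One set of inputs (0.2 SD shift, correlations 0.6 to 0.9) gave 24% to 32%. Such a figure depends on whether baseline is in the model and on inputs the protocol does not give.

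**Conclusion.** The point holds for the repeated ordinal respiratory outcome, and for fever only if fever is modelled as a repeated daily response. As written, section 12.3.2.3 names two incompatible targets, and its last sentence yields a treatment effect conditional on the previous state, which is not the total effect that section 4.1 seeks.

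The log odds ratio moved toward no effect in all six non-null scenarios of the main check, by 10% to 44%. The loss was largest when treatment acted early and symptoms then persisted. The direction agreed under both sets of assumptions; the size is assumption-dependent. With no treatment effect, both coefficients stayed near zero, so type I error is not inflated. Power was little changed in simulated trials of 492 per arm. The analysis is secondary; the primary model and the hospitalisation comparison are untouched. The sentence should be corrected, but it does not threaten the trial's main conclusion.

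**What to change.** In section 12.3.2.3, replace the sentence on time-dependent covariates. State that the model adjusts for the baseline symptom response and other variables fixed before randomisation, for example those already named for the primary analysis in section 12.3.1. Keep visit as a factor, stratification by site, the working correlation and robust standard errors. State whether the reported odds ratio is visit-specific or overall, and whether fever is analysed as a daily response or as one total per patient.

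If a lagged-response model is still wanted, label it supportive and either state its conditional estimand or average its results back to time-specific probabilities by arm.

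The cost is one or two sentences in the protocol, mirrored in the statistical analysis plan before database lock. No extra patients, visits or data are needed.

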#### **12.3.3. Pharmacokinetic Analysis**

Sparse PK from DBS will be analyzed using standard population PK analysis methodologies using standard software such as NONMEM® V7.4 or Phoenix NLME V8.2.

#### **12.3.4. Exploratory Exposure-Response Analyses**

PK-evaluable participants will have post-hoc individual concentration profiles and exposure estimates determined for exploratory exposure-response analyses against primary and secondary efficacy and safety endpoints. Exploratory PK/pharmacodynamic analyses will be performed as the data allow.

#### **12.3.5. Combined Study Analysis**

This protocol is being published as a model protocol for other institutions to consider as they undertake studying treatments to prevent development of LRTI among outpatients with SARS-CoV-2 infection. It is hoped that individual patient data from similar studies can be pooled into a combined study analysis. De-identified data from the present study will be made available for these purposes in accordance with the funder's open access policy (<https://www.gatesfoundation.org/how-we-work/general-information/open-access-policy>).

### **13. Reimbursement**

#### **13.1. *Reimbursement in Brazil***

No reimbursement will be made in Brazil.

